# A single-centre randomised, feasibility study using point-of-care (POC) testing for respiratory viruses to direct oral corticosteroids use in preschool-aged children with acute wheeze: a protocol

**DOI:** 10.1186/s40814-026-01786-x

**Published:** 2026-02-24

**Keywords:** Preschool wheeze, Point of care, Viral testing, Oral corticosteroids

## Abstract

**Background:**

Wheezing in the pre-school aged group (under 5 years) is a common presentation and significant healthcare burden. It is a heterogenous presentation representing a spectrum of phenotypes, and although the causes may be multifactorial, viral infection is the most common trigger, with rhinovirus and Respiratory Syncytial Virus (RSV) being the most commonly detected. Rigorous evidence-based guidance for the acute management of preschool wheeze (PW) with respect to which children are likely to benefit from oral corticosteroid therapy (OCS) is lacking. RCTs of OCS use in PW have not adequately assessed the impact of respiratory virus testing in the management of PW. In order to address the hypothesis that OCS response may be determined by the specific virus in a future definitive trial, the feasibility of performing POC respiratory virus tests prior to randomisation in an acute paediatric ED setting needs to be ascertained.

**Methods:**

The PRECISE Study will be a single centre, randomised, open-label, feasibility trial. Children aged 24–59 months with acute wheeze will be eligible if the clinician is uncertain if there is a role for oral corticosteroid therapy or not. At enrolment, participants will undergo a nasal swab for rapid respiratory virus testing. Children will be randomised in a 1:1 ratio to receive oral dexamethasone or not, based on their RSV result. Participants will continue to be managed by the clinician according to local guidance. They will be invited for clinical review at 72 h where a repeat nasal swab may be performed. There will be a telephone follow-up at 1 month and parents will be invited for extended telephone interviews within a further month. Comprehensive screening logs will address the primary outcome of recruitment and timeliness until enrolment. Remaining timeliness and adherence outcomes will be recorded in individual participant records and described using CONSORT diagrams. Acceptability will be measured using both qualitative and quantitative approaches based on the theory of acceptability framework.

**Discussion:**

This pragmatically designed trial will address key feasibility points needed to inform a future, definitive multi-centre RCT prospectively testing the role of respiratory virus testing to randomise children with PW to receive oral corticosteroids or not.

**Trial registration:**

Clinicaltrials.gov ID NCT06580600.

## Background and rationale

Wheezing in early childhood is very common, with over half of all children anticipated to have one episode of Preschool Wheeze (PW) by their sixth birthday [1, 2]. In the UK, cohort studies have consistently demonstrated a high prevalence of PW, with a recent increase in acute presentations [3, 4]. Wheezing in the pre-school aged group is a heterogenous presentation representing a spectrum of phenotypes and multifactorial pathophysiology [1, 2]. Viral infection is the most common trigger of acute PW. The most commonly implicated viruses are rhinovirus (RV) and Respiratory Syncytial Virus (RSV), each accounting for approximately a third of all infections [5].

Oral corticosteroids are extensively used in the management of PW, despite little robust evidence to support their ubiquitous use. Randomised controlled trials evaluating systemic corticosteroids in preschool children with acute wheeze have produced heterogeneous and largely conflicting results, reflecting differences in age, setting, wheeze phenotype, and viral aetiology. A recently published meta-analysis, including twelve PW trials conducted over the past two decades, failed to find a clinically meaningful benefit for OCS in PW. They were able to report a small reduction in wheeze severity at 4 h (2.6%) but this was not sustained at 12 h; they were also able to report a reduction (approximately 3 h) in total hospital length of stay for children receiving OCS [6]. Only three of these twelve trials reported findings according to viral pathogen; the majority of participants were analysed post-hoc and underpowered to draw comparisons between virus aetiology [7–9].

One challenge of conducting clinical trials of OCS for children with PW is differentiating this from bronchiolitis. There is good evidence that OCS is not effective in the treatment of RSV-induced bronchiolitis, the commonest cause of wheezing and LRTI in under 2-year-olds [10, 11]. In previous studies of PW it has not been possible to prospectively exclude infants with proven RSV infection. This has led to many trials including infants with RSV infection, potentially masking the benefit of OCS for children with wheeze not due to RSV bronchiolitis.

Point-of-care respiratory viral testing is common in healthcare settings with results available within minutes [12, 13]. However, it remains unclear if POC respiratory viral testing can be used in a clinical trial setting to exclude children with RSV from a clinical trial of OCS for PW.

We hypothesise that in children with mild-to-moderate acute PW, not associated with RSV, the use of OCS improves respiratory outcomes. To address this hypothesis in a definitive trial, the acceptability and feasibility of performing POC respiratory pre-randomisation needs to be ascertained. The PRECISE Study is a single centre randomised trial to assess the feasibility of performing POC respiratory viral testing prior to OCS randomisation.

## Aims and objectives

The overall aim is to inform the design of a future, definitive, multicentre RCT comparing OCS to no OCS for acute PW, using POC respiratory viral testing to selectively identify and cohort eligible participants.

### Primary objective

To evaluate the feasibility of randomisation to receive OCS or no OCS treatment based on POC viral testing results in pre-school aged children with wheeze in a paediatric ED setting.

### Secondary objectives

To evaluate barriers to enrolment of patients in a future, definitive trial.To describe viral aetiology of preschool wheeze in the included cohort.To assess parent/guardian acceptability of using a viral POC test in ED to formulate a management plan for PW.To assess the feasibility of obtaining a second follow-up nasal swab (NS) and achieving follow-up at specified time points.

### Exploratory objectives

To assess the feasibility of obtaining finger prick blood tests for POC testing of peripheral blood eosinophil counts in a paediatric ED setting.Describe peripheral eosinophil count values in patients undergoing optional testing.

## Trial design and setting

This feasibility study will be conducted as a single-centre, prospective, randomised open-label study. The flow diagram depicting an overview of the study, including the optional components of the study, is presented in Fig. 1. The study site will be solely the Royal Belfast Children’s Hospital, (RBHSC). Recruitment will take place in the RBHSC Emergency Department (ED).

**Fig. 1 Fig1:**
[figure not shown]
Summary of flow of participants through the PRECISE Study. Created with BioRender.com

### Population/eligibility criteria

Participants meeting study eligibility criteria by age and clinical diagnosis will be entered anonymously into a screening log in the ED. Eligibility will be confirmed by a member of the clinical team using the eligibility criteria and subsequently confirmed by a member of the research team who is named on the delegation log.

### Inclusion criteria

Aged 24–60 months.-Clinical diagnosis of acute wheeze.

### Exclusion criteria

OCS definitely required following clinician assessmentOCS definitely not required following clinician assessmentSigns and symptoms of severe or life-threatening wheeze (Table 1)

**Table 1 Tab1:** Summary of wheeze severity. (Adapted from BTS/SIGN guidance) [14]

Features on presentation	Moderate Acute Wheeze	Severe acute Wheeze	Life threatening wheeze
Signs and Symptoms	Able to talk freely,	Too breathless to feed or talk, Absence of life-threatening wheeze Severe work of breathing	Exhausted, Poor respiratory effort or silent chest, Hypotension, Decreased conscious level, agitated or confused, Cyanosis,
Oxygen saturations in air	O2 ≥ 92% in air	O2 < 92% in air	Oxygen < 92% and clinical signs abovePatients presenting with wheeze suspicious for a non-respiratory causeClinical evidence of shock (e.g. prolonged capillary refill time greater than 3 s)Clinical evidence of bacterial sepsis as indicated by the RBHSC sepsis screening toolPast history of severe or life-threatening asthma or history of previous intensive care admission with acute wheezeHistory of preterm birth (before 30 weeks gestation) or with a diagnosis of chronic lung diseaseKnown immunodeficiency/ongoing immunosuppressive therapyContraindication to oral corticosteroidsPreviously enrolled in the PRECISE StudyChild not assessed by paediatric clinician acting as decision maker on the middle grade rotaRefused POC nasal swab testing

## Consent and enrolment

Potential participants will be identified by clinicians and invited to speak with a member of the research team. The research team will then approach the parent/guardian(s) of potentially eligible patients, confirm eligibility, provide written participant information, and discuss the trial. This includes detailing the optional components of the study and the potential to use nasal swab samples in ancillary studies. A screening log of all patients meeting the inclusion criteria will be maintained and constructed based upon the SEAR framework [15].

The parent/guardian(s) of potentially eligible patients will be allowed a maximum of 60 min to decide if they wish their child to be included in the trial. Written consent will be taken by an authorised member of the training log, from a legal parent/guardian(s) on behalf of the participant. The consent form clearly denotes the use of swabs. A log of those declining consent, including the reasons for this, will be maintained.

## Study procedures

### Nasal swab event

Sampling for respiratory virus testing will occur at initial presentation and at the 2-day follow-up. Nasal swabs will be performed by the research team in a standardised method using a minitip flocked swab (COPAN ITALIA SpA) in each nostril. The material will initially be tested using the cobas® liat system [Roche Diagnostics], which uses a multiplex RT-PCR assay for rapid detection of RSV and influenza A/B. Residual material will be sent to the Regional Virus laboratory for identification of any additional viral pathogens (SARS-CoV-2, seasonal coronaviruses, rhinovirus, adenovirus, human metapneumovirus and parainfluenza viruses). Any remaining residual nasal swab material will be frozen and stored for further analysis of airway immune responses at Queen’s University Belfast (QUB). All samples transferred to QUB will be anonymised prior to transfer. Nasal swabbing is commonly performed for children being admitted to hospital and will be performed by experienced practitioners to minimise any discomfort/distress for the participant and their parent/guardian(s).

### Finger prick eosinophil count

For participants who consent to optional finger prick blood testing for peripheral blood eosinophils (PBE), this will be performed at the same time as the nasal swab. PBE counts will be obtained using POC testing on the Hemocue® WBC DIFF device [Accuscience], which provides a 5-point full white cell differential result.

Results of the POC tests, extended viral testing, and peripheral blood eosinophils will be made available to the family and their clinical team, who are familiar with interpreting and actioning such results, and documented by the research team in the child’s medical record.

### Randomisation and allocation

Participants will be randomised using an automated web-based system using permuted blocks in a 1:1 ratio according to RSV test results. Randomisation will be completed on the REDCap platform, used for the completion of electronic Case Report Forms (CRF) by an appropriately trained and delegated member of the research team. The allocation sequence is designed by the trial co-ordinator and will not be shared with wider teams to avoid prediction of randomisation and selective enrolment.

### Blinding

Parents/guardians, those who provide health care to the participants, and outcome assessors will not be blinded to the allocated intervention. This includes the study statistician, who has no role in decision-making with regard to the conduct of the study, and the remainder of the research team will also be unblinded for the purposes of managing data collection and reviewing cases to assess for protocol deviations.

## Intervention

Oral corticosteroid is usually given in the RBHSC ED as oral dexamethasone (typically 0.3 mg/kg). It is given as a single dose; therefore, adherence is not an issue in the acute setting. If the participant vomits within 30 min of dexamethasone administration, it may be re-administered at the discretion of the treating clinician and recorded in the CRF. The unblinded clinician may choose to determine the OCS therapy plan at any point after enrolment, irrespective of allocation (e.g. prescribe OCS to a child randomised not to receive OCS). Any deviation from planned study randomisation will be recorded on the CRF. After randomisation, participants will continue to follow this RBHSC guideline; there will be no further difference in-between arms. Clinicians may perform investigations and administer additional treatment according to local hospital guidance. These, and any other concomitant medications, will be recorded on the CRF.

## Outcome measures

### Primary outcome measures

Recruitment: the proportion of eligible patients that are enrolled following screening and the reasons for not recruiting eligible patients.Adherence: The proportion of enrolled patients remaining in allocated treatment.Timeliness: Time (minutes):◦ From triage to clinician decision regarding eligibility to enrolment.◦ From screening until the availability of POC test results.◦ From screening to documented time of randomisation.◦ From screening to documented time of OCS administration (if applicable).◦ From screening to discharge from department.Acceptability.◦ Parent/guardian feedback regarding the process of randomisation and enrolment using a mixed method qualitative approach.◦ Parent/guardian feedback regarding the acceptability of POC testing on their children using a mixed method qualitative approach.

### Secondary outcome measures

Proportions of patients with positive respiratory viral testing results for RSV and/or other respiratory viruses, or no virus detected.Proportion of discordant viral swab results between consecutive tests in the same patient.•Proportion of enrolled patients completing second nasal/NP swab, follow-up assessments, and completeness of recording of follow-up information.

### Exploratory outcome measures

Proportion of enrolled patients completing optional finger prick blood testing.Description of mean peripheral eosinophil count values in enrolled patients.

## Data collection and assessment schedule

Overall, the study incorporates three follow-up points per participant as summarised in the schedule of assessments (Table 2). UK BTS/SIGN guidance recommends all patients presenting with acute asthma or wheeze should be reviewed following discharge from ED/hospital within two working days [14]. Participants will be offered an in-person review with a clinical member of the research team within two working days (± 1 day) in the ED department. This review will include a brief, standardised clinical assessment and clinical data will be collected in line with standard care for ED review visits.

**Table 2 Tab2:** Schedule of assessments

	ED attendance	Time from enrolment			
		2 working days ± 1 day	28 days	< 60 days	
			(*degree of flexibility*)		
Screening and data entry to screening log	X				
Provision of study materials to eligible patients	X				
Informed consent process	X				
Nasal Swab Event (NS)	X	X			
Randomisation and OCS administration (creation of CRF for enrolled patients)	X				
Notes review and CRF checking by member of research team		X	X		
Notes review and CRF completion by member of research team			X		
In person review (RBHSC, ED)		X			
Optional fingerpick blood test	X	X			
Parent telephone calls by member of research team			X		
Adherence to randomisation reviewed	X	X	X		
AE reporting	X	X	X		
Invitation to take part in qualitative interviews			X		
Optional Qualitative Interviews					X

The parent/guardian(s) will be telephoned by a member of the research team approximately 28 days after enrolment to complete a survey about participant outcomes as well as adherence and initial review of trial acceptability. This review will be pre-scheduled with the parent/guardian(s) at the day 2 appointment. If a participant does not present for planned in-person review, the research team will aim to contact parent/guardian(s) up to three separate times by telephone on the same day. If unsuccessful, they will try the following day or using an alternative phone number if provided. If still unsuccessful, an email invitation to contact the research team will be sent. If no further contact is achieved, the participant will be marked as lost to follow-up. Remuneration for the burden of time caused by the PRECISE Study will be provided to the families through the use of an online gift voucher sent by email.

All data will be collected and recorded in electronic case report forms (CRF) within a bespoke, web-based, electronic platform using REDCap software [16]. Hard copies of consent forms will be used, and kept securely alongside the participant linkage log. The screening logs and electronic CRFs will capture data pertaining to the primary outcomes. The screening log will capture the recruitment rates and the timeliness of patient flow through the trial up to recruitment and randomisation. The remaining timeliness data will be captured in individual CRFs alongside adherence over the three time points in the study period.

Acceptability of the trial interventions will be measured using a ten-point questionnaire based on the Theory of Acceptability framework [17]. This will be sent electronically to parents/guardians on day 2 and day 28 review, but it can be read out to people without access to emails or difficulties reading. Additionally, parent/guardian(s) of enrolled patients will be invited to participate in exploratory qualitative interviews within 2 months of enrolment.

### Data management and confidentiality

Participant data will be held within the secure REDCap platform linked to Queen’s University Belfast. The research team and site staff will undergo training to ensure all data is accurate, complete, and reliable. Quality is also assured through the use of REDCap software allowing a full audit trail, consistency, and compliance with GCP and relevant regulatory requirements [16]. For routinely collected clinical data from clinical records, researchers will use the participant study number (PSN) assigned at randomisation to link data pseudo—anonymously. Regular data review will be carried out by the study co-ordinator and PI to ensure consistency and identify any discrepancies or protocol deviations. Additionally, quality control will be ensured by the use of Standard Operating Procedures (SOPs) of the Belfast Trust. Data will only be accessed by delegated members of the research team, a list of which will be kept in the Study Master File (SMF). All essential documents including participant consents and linkage logs will be stored in a study file in locked cabinets according to Belfast Trust data storage and archiving guidelines.

## Sample size and recruitment

The PRECISE study will recruit a minimum of 30 participants testing positive for RSV and 30 participants testing negative for RSV. However, as RSV status will be determined after enrolment, the PRECISE Study has the capacity to enrol up to 150 participants to ensure minimum requirements are met.

A target of 30 participants per group is in line with literature for feasibility studies using mixed methodology [18–20]. In order to truly address the primary outcome of acceptability in this feasibility study, it is imperative that the voice of families is represented. A minimum of 60 participants was informed by an anticipated attrition rate to complete surveys (50%) and uptake of qualitative interviews (15%) from previous studies [21]. This needs to be achieved in both treatment arms to ensure that adherence is not different depending on viral status. Feasibility of achieving this target is supported by local audit data of ED attendances in previous winter seasons.

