## Data analysis and criterion for assessing feasibility of trial

The progress of all eligible participants will be described, from screening to completion of the study, using a CONSORT flow diagram. Descriptive statistics for continuous variables (mean, interquartile ranges) and categorical variables (frequency counts, percentages) will be used to summarise baseline characteristics of screened and enrolled patients. Potential barriers to recruitment will be investigated by comparing the descriptive statistics between those recruited and those eligible but not recruited using chi-squared or Fisher’s exact tests for categorical data and Mann–Whitney U tests for continuous data. The proportion of participants who successfully complete consent, randomisation, receipt of intended treatment allocation, and evaluation for each objective will be described as percentages of the total number screened for eligibility and approached. The reasons given for not recruiting eligible patients will be collated and described. The proportion of enrolled patients remaining in their allocated treatment arm will be described as percentages of the total number randomised. The time taken for each stage of patient flow will be described as medians (with interquartile ranges) and graphically using Kaplan–Meier plots.

Qualitative interview data will be transcribed internally, checked, and anonymised as the study progresses. QSR NVivo software will be used to assist in the organisation and indexing of qualitative data. Data will be analysed thematically, and analysis will be informed by the constant comparison approach of grounded theory [22]. Both the interview topic guides and the parental surveys have been adapted from the framework of acceptability to facilitate a robust analysis to address acceptability outcomes [17]. Parent/guardian(s) will complete surveys prior to the additional interviews, and their responses will be available to the interviewer. This is designed for triangulation of survey responses; however, the interviews will be able to support the development of new ideas, particularly regarding ways to improve the study design, and may identify themes beyond the framework which may not have been identified by the researchers.

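### Thirty RSV-positive and 30 RSV-negative children can describe but not ensure equal adherence by viral status, and no stated adherence criterion is split by RSV status

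*Protocol article*

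**What the plan says.** The protocol article (Sample size and recruitment) sets its minimum by test result: "The PRECISE study will recruit a minimum of 30 participants testing positive for RSV and 30 participants testing negative for RSV". It adds that "the PRECISE Study has the capacity to enrol up to 150 participants to ensure minimum requirements are met". It then gives a reason that concerns adherence: "This needs to be achieved in both treatment arms to ensure that adherence is not different depending on viral status". The only numerical inputs in that section are 50% survey attrition and 15% interview uptake, and both bear on acceptability. No adherence rate, margin or precision target is given.

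Children are randomised by "permuted blocks in a 1:1 ratio according to RSV test results" (Randomisation and allocation), so RSV status is known for every randomised child.

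Adherence is defined under Primary outcome measures as a single proportion of enrolled patients. The analysis section says: "The proportion of enrolled patients remaining in their allocated treatment arm will be described as percentages of the total number randomised". In Table 3, Green needs at least 80% and Amber at least 70% of patients to remain in their allocation. Red applies when more than 25% of those allocated to no OCS receive it before the day 2 visit.

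**The concern.** The sample-size section gives the two RSV groups a purpose that neither the analysis nor the progression criteria take up. Two questions follow: can 30 against 30 support a statement that adherence does not differ, and could a problem in one RSV group go unnoticed in the traffic-light assessment?

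A difference by RSV status is plausible. Treatment is open label, test results "will be made available to the family and their clinical team", and the clinician may depart from the allocation at any point (Intervention). What is at stake is the progression decision. The hypothesis for the definitive trial concerns wheeze not associated with RSV (Background and rationale; Discussion), so adherence among RSV-negative children is the number that trial would rely on. A total over both groups mixes in RSV-positive children, in a ratio fixed only by two minimums and a cap.

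**Working it through.** **Inputs.** From the article: 30 children per RSV group as the minimum, cap 150, 1:1 allocation by RSV result, Green 80%, Amber 70%, Red above 25% crossover from no OCS. Assumed: about 15 children per RSV-by-arm cell at the minimum size, thresholds as printed, and true adherence values as stated in each step.

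**1. The plan's own figure.** 30 + 30 = 60. At 50% attrition this gives 60 × 0.5 = 30 surveys; at 15% uptake, 60 × 0.15 = 9 interviews. No calculation for adherence is given, so there is none to reproduce.

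**2. What 30 against 30 can say.** With 80% adherence in each group, the 95% half-width for the difference is 1.96 × √(0.8 × 0.2/30 + 0.8 × 0.2/30) = 0.202, about ±20 points. Within one treatment arm (15 against 15) it is 1.96 × √(2 × 0.8 × 0.2/15) = 0.286, about ±29 points. One group at 24/30 has an exact 95% interval of 61% to 92%.

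**3. The Red rule as a guard.** With 30 no-OCS children, 7/30 = 23.3% is not Red and 8/30 = 26.7% is. A problem can therefore stay hidden only if there are at most 7 no-OCS crossovers, with any other departures in the OCS arm.

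**4. Examples inside that limit, at 30:30.**
- 28/30 + 20/30 = 48/60 = 80%: Green, with one group at 67%, below the Amber floor. There are 12 departures, so at least 12 − 7 = 5 must be OCS-arm children.
- Seven crossovers, all in one RSV group, and no other departures: 7/15 = 47% crossover in that group's no-OCS arm. The total is 53/60 = 88%, Green, and 7/30 is not Red.

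**5. How often.** Suppose true adherence is 95% in one group and 65% in the other, with 15 per cell, and let *s* be the share of non-adherence that falls in the no-OCS arm. A group with non-adherence *q* then has no-OCS non-adherence 2*qs* and OCS non-adherence 2*q*(1 − *s*). Adding exact binomial probabilities over all outcomes with at most 12 departures and at most 7 crossovers gives:

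| *s* | P(Green total, Red not met) | of which weaker group observed below 70% |
|---|---|---|
| 50% | 54% | 21% |
| 75% | 24% | 5% |
| 90% | 6% | 0.2% |
| 100% | 2% | 0% |

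**6. Dependence on the mix.** If a share *w* of randomised children is RSV-positive, the lowest RSV-negative adherence compatible with an 80% total is (0.8 − *w*)/(1 − *w*), reached when every RSV-positive child adheres. This is 60% at *w* = 1/2, 70% at *w* = 1/3 and 75% at *w* = 30/150. Concentrated crossover can still go unflagged at the last mix: of 75 no-OCS children, 18 crossovers (24%) is not Red, yet 18 of the 60 RSV-negative no-OCS children is 30%.

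**The case against.** The strongest objection is that Table 3 does not simply pool everyone. Red is specific to the no-OCS arm, and the Intervention section's own example of an override is giving OCS to a child allocated not to receive it. If departures are mostly of that kind, Red catches most of the bad cases, as the table in step 5 shows. This stands. A reader might infer that a failing RSV group would usually be hidden behind a Green total; the document does not support that.

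A reader might also infer that adherence will differ by RSV status, or that RSV-negative children will do worse. No figure in the article supports either, and eligibility already requires clinician uncertainty about OCS. A difference is plausible, no more. The Background puts RSV at about a third of infections. With a mix near that share, a Green total could not coexist with RSV-negative adherence below 70%. The article fixes no mix, however, and the minimum design is 30:30.

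Thirdly, a feasibility study need not be powered for this comparison, and the article states no test, margin or power. That is right, and low power is not the complaint. The complaint is that the sentence promises a property that the design cannot deliver.

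Finally, a breakdown by RSV group might be planned in a fuller document. Table layout can be left there. But the article itself fixes the denominator and the thresholds, and these do not serve the purpose that it states for its sample size.

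**Conclusion.** The point holds in a limited form. Thirty against 30 describes a difference in adherence to within about ±20 points and cannot ensure that there is none. The adherence outcome, analysis and Green and Amber thresholds are not split by RSV status, and Red is split by arm only. At the minimum size a Green total can therefore coexist with an RSV group at 67%, or with 47% crossover in one group's no-OCS arm, as long as no more than 7 of 30 no-OCS children cross over.

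This rests on about 15 children per cell and on thresholds as printed. The 10% margin attached to the progression rule has no stated direction. If it relaxes the thresholds, masking is easier. If it raises the adherence threshold to 88%, the 48/60 example no longer passes while 53/60 (88.3%) does; at 90% neither passes. Separately, the quoted sentence speaks of treatment arms where the section sets its minimums by RSV result, and the Green recruitment criterion in Table 3 also counts 30 per arm. The wording should be reconciled.

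**What to change.** - In Sample size and recruitment, replace the claim to ensure no difference with a statement such as: *adherence will be described by viral status (95% CI for the difference about ±20 percentage points at 80% adherence)*. Refer to the RSV groups instead of treatment arms.
- Report adherence and crossover in the four RSV-by-arm cells with exact 95% intervals, and give the difference by RSV status with its interval.
- Apply the Table 3 adherence criteria, including the Red crossover rule, to the RSV-negative group as well as overall. Recruitment is under way, so fix this before adherence results are examined.

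**Cost.** One table, one reworded sentence and one added line to the criteria. RSV status and adherence are already recorded, and no extra children are needed. The group estimates will be imprecise, as step 2 shows, and Green becomes somewhat harder to reach. With 15 RSV-negative no-OCS children, 4 crossovers (27%) would meet the Red rule, so the interval should be read beside the colour.
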